**Table 3. Sampling strategy for use-cases semi structured interviews:**

| Use case and participant group              | Sampling strategy                                                                        | Estimated number of semi-structured interviews |
|---------------------------------------------|------------------------------------------------------------------------------------------|------------------------------------------------|
| 1. Health care workers                      | 10 participants from self-testing and 10 participants from diagnostic testing facilities | Estimate 20 people (saturation)                |
| 2: Outbreak                                 | 5 recruited per outreach site from 4 different locations                                 | Estimate 20 people (saturation)                |
| 3: Primary care facility OPD                | Recruit 10 participants from 2 sites                                                     | Estimate 20 people (saturation)                |
| 4: Secondary distribution of self-test kits | Interview index patients (those that agree to linkage/ follow up).                       | Estimate 20 people (saturation)                |
| Totals                               |                                                                                          | 80 interviews                           |

## 5.5. Costing and cost-effectiveness

The one-off testing models of COVID-19 testing, and self-testing will be fully costed to provide cost data that may be anticipated under programmatic implementation for policy makers. Therefore, this cross-cutting component aims to collect cost data that will be essential to cost and cost effectiveness analyses, to be used in the cost section of the process evaluation.

### Objectives:

1. To conduct costing of the implementation models
2. To compare costs and cost-effectiveness between period before and during implementation for the OPD model
3. To undertake economic modelling to estimate the impact of the different models.

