#### **Overview**

The 12 health facilities used for the health care worker use case will also be selected for implementation and evaluation of the OPD use case. The sites will be selected on the basis of having at least 100 health care workers and therefore high throughput for outpatients i.e., also serving more than 100 outpatients in any given day. Patients who test positive will be offered confirmatory testing and care under national guidelines. Training for use of existing and/or new Ag-RDTs will be provided to staff before implementation commences.

Routine provider-delivered diagnostic services using COVID-19 Ag-RDTs will be supported by PSI and District Health Office, Blantyre for patients presenting to clinics with symptoms of COVID-19 according to Malawi case-definitions and testing criteria. Services will be aimed at decentralising testing and meeting peak-testing demands during epidemic waves as part of facilitating early detection and enable effective infection prevention and control, including linkage to appropriate COVID-19 care.

We aim to offer COVID-19 testing to OPD attendees first by introducing the study while they wait for clinical consultation in a group and secondly one-on-one through a study introduced screen where sampling and testing will occur (Figure 2).

[figure not shown]

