### **Sample size**

We conservatively assume that 70% of participants across clinics will accept to be tested for COVID-19. For the sample proportion to be estimated to within  $\pm 0.05$  (5%) using the 95% confidence level, a sample of 323 participants would be required.

However, we assume the following:

- i. Integration of COVID-19 testing into routine health services will be maintained for the foreseeable future but will target people with symptoms of COVID-19 and for those who are at high risk for severe COVID-19.
- ii. We also assume, based on precedent, that low proportions will test positive outside of an epidemic wave, with each epidemic wave lasting 6 weeks, and we expect 2 waves within the study period.
- iii. We assume that each facility serves at least 100 OPD attendees per day, of whom at least 30% will have one or more COVID-19 symptoms, and that 70% of those eligible will accept SARS-CoV-2 testing i.e., 21 attendees could accept testing per day over 12 sites, totaling a potential study population of 252 in any one day, or 7,560 per 6week wave.

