#### **Main analysis**

A programmatic evaluation and analysis of data will report on the proportion of participants accepting to be tested, tested positive and those linking to care and treatment. A descriptive process evaluation will analyze month-by-month the numbers of COVID-19 tests conducted at each facility before introducing COVID-19 Ag-RDTs. Once Ag-RDTs are made available, numbers accepting the test, and numbers diagnosed Ag-RDT+ve will be collected. Denominators will be all clinic attendees.

Time trend analysis will be used for descriptive analysis of trends in numbers (%) of all attendees screened for symptoms, reporting one or more COVID-19 symptom, identified, and tested for COVID-19, and the number/percentage of those testing positive. Data will be reported for all patients, and for all patients who would be eligible for antiviral treatment if tested positive.

Descriptive analysis of the proportion of participants and binomial exact 95% CI accepting to test, testing positive and accepting next steps for COVID-19. The proportions will be stratified and compared either using t-test or Chi-square test for continuous and categorical variables accordingly.

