## Outcomes

- i. Cost per kit distributed
- ii. Cost per kit used
- iii. Cost per positive patient diagnosed
- iv. Cost per positive patient diagnosed and linked to prevention and care
- v. Cost per COVID-19 infection and death averted
- vi. Cost of scaling-up COVID-19 self-testing

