baseline questionnaire for index case) shall be used to interview index cases who tested positive for COVID-19 from any of the use cases at time of testing positive. The questionnaire will collect information on social demographic indicators about the index, COVID-19 symptoms, risk and testing, and information about their close contacts. Another structured questionnaire (Appendix 17- CC02: Index case follow up questionnaire) will be used to interview index cases 7-14 days after recruitment to follow up on each of their listed contacts.

For the qualitative process evaluation study, semi-structured topic guides shall be used to interview clients from OPD, congregate settings (Appendix 18: Client process evaluation qualitative interview guide), implementers (study coordinators, investigators and frontline implementers) (Appendix 19 - CK01: Process evaluation among key informants) and HCW (Appendix 20 - Providers SSI topic guide) in PIC arm who would have completed the three months follow-up period to assess the acceptability, adoption, appropriateness, costs, feasibility, fidelity and penetration of the intervention.

For the cost and cost effectiveness study, a structured questionnaire (Appendix 22 - Facility costing data collection tool) shall be used to interview clinic managers on: costs of overhead supplies (utilities, facility supervision, administrative, cleaning, security and transport costs); and COVID-19 testing costs (Ag RDT or PCR). The tool shall also be used to assess rooms, equipment, furniture, staffing, consumables and equipment used for each COVID-19 testing service, and time and motion for staff providing COVID-19 testing services. A semi-structured interview guide shall be used to ask clients about the time spent at the clinic and any costs incurred in accessing COVID-19 testing.

For the costing component: We will conduct exit interviews (Appendix 23: Client cost exit questionnaire) on 100 purposively selected testers across all use cases. The exit interviews will be aimed at collecting costs of accessing COVID-19 testing. We will ask participants to estimate the amount of time taken and costs incurred to access testing. For the OPD model, we will collect the user costs before and after the intervention to allow for a before and after analysis. This will enable the estimation of opportunity cost to testing both as direct out-of-pocket payments (direct costs) and lost income (indirect costs).

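### On its per-positive outcomes, the outpatient (OPD) before/during cost-effectiveness comparison cannot separate the testing model from the timing of the epidemic

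*Protocol*

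**What the plan says.** Section 5.5 (Objectives) plans "To compare costs and cost-effectiveness between period before and during implementation for the OPD model". The OPD objective in section 5.1.2 also announces a cost-effectiveness comparison but names no comparator, so 5.5 is where the contrast is fixed. Section 5.9 (Overall data tools) adds: "For the OPD model, we will collect the user costs before and after the intervention to allow for a before and after analysis".

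On sites, section 5.1.2 (Overview) says: "The 12 health facilities used for the health care worker use case will also be selected for implementation and evaluation of the OPD use case". This includes the six facilities that serve as standard of care in the health care worker study, so none is held back as an OPD control.

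The six outcomes in section 5.5 include "Cost per positive patient diagnosed", the same cost restricted to positives linked to prevention and care, and cost per infection and death averted. The others are cost per kit distributed, cost per kit used and the cost of scaling up.

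On the epidemic, section 5.1.2 (Sample size) assumes "low proportions will test positive outside of an epidemic wave, with each epidemic wave lasting 6 weeks, and we expect 2 waves within the study". The only planned handling of time is in section 5.1.2 (Main analysis): "Time trend analysis will be used for descriptive analysis of trends in numbers (%) of all attendees screened for symptoms", continuing through to numbers tested and testing positive. Section 5.5 mentions no adjustment for incidence or positivity, no matching of calendar periods and no control series.

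**The concern.** Cost per positive is cost per test divided by positivity. Positivity depends partly on who is offered a test, which the model can change, and partly on how much SARS-CoV-2 is circulating, which it largely cannot. A before/during comparison in the same 12 facilities changes both together. The protocol predicts that the second component will move a great deal during the study, yet it sets up a contrast that has no means of separating the two.

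Section 5.5 says the costing is meant for policy makers, and section 5.12 says findings are aimed first at the Ministry of Health. If implementation carries more wave time than the pre-period, the model would look efficient on cost per positive even if nothing else had changed. If the pre-period carries more, it would look wasteful. A reader of the report could not tell which part of the difference belonged to the programme.

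**Working it through.** **The plan's own figures.** The protocol gives no number for the before/during comparison. The nearby inputs reproduce:
- Testing volume (section 5.1.2): 100 attendees × 0.30 symptomatic × 0.70 accepting = 21 per facility per day; × 12 facilities = 252 per day; × 30 working days = 7,560 per six-week wave. The 30 days are inferred from the stated total and correspond to a five-day week.
- Positives (section 5.1.4): 30,000 tests × 0.02 = 600 index cases. This 2% is an average over all use cases, not an out-of-wave value.

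**Formulas.** With cost per test C, positivity p and proportion linked L:
- cost per positive = C / p
- cost per linked positive = C / (p × L)

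If C and L are the same in both periods, the during/before ratio of either outcome is p(before) / p(during), whatever the value of C.

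**Assumptions for the illustration** (none is a document figure except the two six-week waves):
- positivity of 2% outside and 10% inside a wave
- implementation lasting 26 or 52 weeks
- equal numbers of tests each week
- the same model and the same cost per test in both periods

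**Case A: both waves fall in implementation, none before.** Wave time is 2 × 6 = 12 weeks.
- 26 weeks: p(during) = (12 × 0.10 + 14 × 0.02) / 26 = 1.48 / 26 = 5.69%. Ratio = 2 / 5.69 = 0.35.
- 52 weeks: p(during) = (12 × 0.10 + 40 × 0.02) / 52 = 2.00 / 52 = 3.85%. Ratio = 2 / 3.85 = 0.52.

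**Case B: one wave in a 26-week pre-period, none during.**
- p(before) = (6 × 0.10 + 20 × 0.02) / 26 = 1.00 / 26 = 3.85%. Ratio = 3.85 / 2 = 1.92.

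**Range.** With 1% to 2% outside and 5% to 20% inside waves, Case A gives ratios from 0.10 (26 weeks, 1% and 20%) to 0.74 (52 weeks, 2% and 5%). Case B gives 1.35 to 5.38.

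**Outcomes less exposed.** Cost per kit and the user access costs in section 5.9 (time, payments, lost income) do not contain p. Cost per test can still move with volume. If a share f of cost is fixed and volume is multiplied by v, the cost-per-test ratio is f/v + (1 − f). For a doubling of volume this is 0.85 at f = 0.3 and 0.70 at f = 0.6 (f and v assumed).

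**Would one common positivity solve it?** At a common p, the ratio is (C1/p) / (C0/p) = C1/C0. It repeats the cost-per-test ratio and rules out, by assumption, any change in yield caused by the model.

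**The case against.** The best counter-argument is that the protocol never assigns a particular outcome to the before/during objective. The outcome list serves the whole costing component, and the only before/after data collection spelled out is user costs, which do not depend directly on positivity. This narrows the point but does not remove it. The objective names cost-effectiveness as well as costs, and the outcomes in the list that measure an effect are per positive, per linked positive, or per infection and death averted.

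A second argument is that other economic evidence is planned. Section 2.3 names no alternative testing and NAAT as comparators, and section 5.5 plans economic modelling. So a reader might infer that the before/during result is the only OPD cost-effectiveness evidence the Ministry would receive; the documents do not support that. Equally, nothing says that the modelling corrects the before/during contrast.

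A third is that standardisation belongs in an analysis plan, and that monthly facility data are already foreseen. The detail could indeed sit there. But the comparator and the roll-out to all 12 facilities are fixed in this protocol, and no later plan can restore a concurrent control.

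A reader might also infer that the model is bound to look good. That does not follow: the pre-period is undated, and Case B reverses the sign. Nor can one quote a rate of false-positive significance tests, because the protocol plans no test of positives between the periods and calls its trend analysis descriptive.

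**Conclusion.** The point holds for cost per positive diagnosed and cost per positive linked. Followed as written, the plan would count a difference in epidemic timing as an effect of the OPD model, in a direction that cannot be known in advance. Under the illustrative assumptions the spurious ratio is 0.35 to 0.52 if both expected waves fall in implementation, and 1.92 if a wave falls only in the pre-period. These sizes rest on assumed positivities, period lengths and even weekly testing. The mechanism rests only on the stated design and the stated expectation of waves.

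The point does not extend to cost per kit or to user access costs. It concerns a secondary economic objective, the last of seven, and leaves the main OPD outcome of test acceptance untouched. The correction is cheap and worth making before the analysis.

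**What to change.** In section 5.5:

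1. Make cost per person tested the before/during contrast for the OPD model. Show testing volume beside it, because fixed costs spread over more tests in a wave.
2. Report cost per positive diagnosed and per positive linked for each period as descriptive, beside monthly positivity for both periods. Section 5.1.2 names monthly test counts for the pre-period but positives only once Ag-RDTs are available, so pre-period positives should be taken from the testing registers already covered in section 6.2.
3. Show the per-positive costs as a sensitivity curve over a stated range of positivity. Do not make a single common-positivity figure the main result.
4. State the dates of the pre-period, and state that the raw before/during difference in cost per positive is not attributed to the OPD model.

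The cost is a few lines of text and a little extra analysis, mostly of data already planned, with no new recruitment. The downside is a less striking headline that is conditional on positivity.

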### Methodological approaches

We will cost the OPD, outbreak and secondary distribution use cases using the iDSI Reference Case for economic evaluation guidelines (i.e., one-off testing models). Health care worker regular self-testing is explicitly **excluded**. The costing will be conducted from a societal perspective using ingredients-based costing approach. We will combine top-down and bottom-up costing approaches:

The bottom-up approach will include a time and motion costing approach aimed at observing staff time allocation on a typical workday, (12 providers in OPD and outbreak investigations), given there are no staff time equivalents with the secondary distribution model, totalling 24 providers.

Time and motion refer to providers working on multiple activities across all use cases. For example, a provider conducting both self-testing and PCR in a healthcare facility. Such a provider will be observed using time and motion studies to determine allocation of personnel time to professional use testing and PCR. The time and motion costing approach is not a new study in its own right, but a method of cost data collection as part of the cost and cost effectiveness component of the project. Written consent will be obtained ahead of the time and motion observations.

We will further conduct exit interviews on 60 purposively selected testers across the OPD, outbreak and secondary distribution use-case. These will be done at exit of the process and will be aimed at collecting costs of accessing COVID-19 testing. We will ask participants to estimate the amount of time taken and costs incurred to access testing. This will enable the estimation of opportunity cost to test both as direct out-of-pocket payments (direct costs) and lost income (indirect costs).

Since we are only interested in costs of accessing testing, we will not include any additional downstream costs including household costs. Written informed consent will be obtained from all participants before the interviews.

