### **2.3. Economics of COVID-19 Ag-RDT testing and self-testing**

The need to consider rational use of resources will be addressed in the current protocol by costing, consideration of service provision efficiencies and estimation of prevention and care impacts to allow incremental cost-effectiveness to be compared against no alternative testing, NAAT testing, and to compare self-test with professional Ag-RDT alternatives.(22) Data on costs and cost-effectiveness of self-testing use cases remain sparse. Costs of accessing testing for COVID-19 in low-resource settings are also limited. The costing component in this protocol will address this data scarcity by evaluating costs of providing and accessing self-testing in comparison to no alternative testing, NAAT testing, and to compare self-test with professional Ag-RDT alternatives. Service integration where self-testing is integrated with Ag-RDT, can also be associated with high time burden on existing staff (23). Understanding such time commitments and considering different varying degree of integration will also be addressed within the protocol.

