|                                             |                                                          |                                                                                   | iii. Sub-sample participant cost interviews, and provider cost observations establishing cost of process                                                                                                                                                                      |                                                                                                                                                                                                                                                                                                                                                           |                  |
| 4. Secondary distribution of self-test kits | Self-testing:
Demonstration project evaluation | Proportion of contacts self-tested for COVID19 (contact uptake of self-test kits) | i. Epi interviews establishing participant sociodemographic profiles
ii. Sub-sample qualitative interviews establishing acceptability of demonstration model
iii. Sub-sample participant cost interviews establishing cost of model ( no provider observations ) | Any positive participant from the use-cases.
All eligibility assessed
i. All receive baseline epi interview, and telephone follow up after 14 days
ii. subsample of 20 qualitative interviews
iii. subsample of 20 patient-level costing interviews

Minimum requirement of 370 contacts to ascertain uptake i | 6,000 self-tests |

|  |  |  |  |  |
|--|--|--|--|--|
|  |  |  |  |  |
|  |  |  |  |  |
|  |  |  |  |  |
|  |  |  |  |  |
|  |  |  |  |  |
|  |  |  |  |  |
|  |  |  |  |  |
|  |  |  |  |  |

MLW: Malawi Liverpool Wellcome Trust Clinical Research Programme; PSI: Population Services International

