#### Cost and cost effectiveness

A subsample of 20 participants will be selected to receive a structured questionnaire asking clients about the time spent testing, and any costs incurred in accessing COVID-19 testing (Patient cost questionnaire\_Final).

A maximum of 12 providers shall also be interviewed and observed through a time and motion approach, ascertaining the costs of overhead supplies (utilities, facility supervision, administrative, cleaning, security and transport costs), COVID-19 testing costs (Ag RDT or PCR), assessing rooms, equipment, furniture, staffing, consumables and equipment used for each COVID-19 testing service, and time and motion (method of collecting cost data) for staff providing COVID-19 testing services (Provider costing data collection tool).

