## **Overview**

There will be a secondary distribution of self-test kits demonstration project to facilitate early detection of positive cases and appropriate linkage to COVID-19 care (home or facility based).

COVID-19 positive patients (index cases) from the HCW, OPD and Outbreak investigation in congregate setting studies will be screened for eligibility and asked for informed consent to participate. The national guidance is that all close contacts of an index case should be deemed positive and treated as such (32). However, the decision to abandon contact tracing in Malawi was largely taken due to the labour and resource-intensive nature of professional Ag-RDTs or PCR for contacts.

This study's approach is to offer COVID-19 self-test kits to the contacts and collect data via the index case, which is relatively inexpensive. Making a generalized assumption that all contacts should be deemed positive may inadvertently put individuals at the front of stigma and economic exclusion.

There are very limited data on COVID-19 secondary distribution in low-and-middle-income-countries and this is a good opportunity to test the model which may as well become the mainstay to manage large testing volumes in times of great demand during COVID-19 waves.

Participants will be provided with brief training on how to demonstrate correct use of nasal swabbing and testing and information leaflets including direction on how to access web-based or WhatsApp video clips.

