### **Exclusion Criteria for index case patients**

Index case patients shall be ineligible for participation if they are

1. Are unable or unwilling to provide informed consent
2. Not traceable or able to be interviewed by telephone
3. Unable to demonstrate back how to self-test correctly

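### The costing plan assumes secondary distribution uses no staff time, yet its procedures need staff for every index case and no tool listed for that use case measures it

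*Protocol*

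**What the plan says.** Section 5.5 (Methodological approaches) describes societal, ingredients-based costing that combines top-down and bottom-up methods. The bottom-up part includes time-and-motion observation of "12 providers in OPD and outbreak investigations". Secondary distribution is left out, "given there are no staff time equivalents with the secondary distribution model", which gives a stated total of 24 providers. The Table 1 entry for secondary distribution agrees: "no provider observations".

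The costing subsections for outpatients (5.1.2) and congregate settings (5.1.3) both state: "A maximum of 12 providers shall also be interviewed and observed through a time and motion approach". The matching subsection of 5.1.4 lists only a questionnaire for 20 participants.

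The procedures in 5.1.4 describe staff work. The Overview says: "Participants will be provided with brief training on how to demonstrate correct use of nasal swabbing and testing". Under Recruitment process, index cases are shown the kits and how to use them and are given kits and masks, and project staff are available by telephone to direct positive contacts to care. One exclusion criterion for index cases is: "Unable to demonstrate back how to self-test correctly".

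Sections 2.7 and 5.5 both promise that this approach will be costed in full. Section 2.3 promises a comparison of self-testing with professional Ag-RDT, notes that "Service integration where self-testing is integrated with Ag-RDT, can also be associated with high time burden on existing staff", and says that such time commitments will be addressed.

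**The concern.** The reason given for leaving staff out of the secondary distribution costing does not fit the model as the protocol describes it. An index case cannot be enrolled and sent away with kits unless a member of staff has given instruction and seen the test demonstrated back. A programme that adopted the model would need at least the instruction and the kit hand-out.

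The gap is one-sided, because labour is observed for professional testing and not for the self-testing alternative. Sections 2.7 and 5.1.4 say contact tracing was given up largely because professional testing of contacts took too much labour and resource. Staff time is therefore the quantity policy makers will want to see. Section 5.5 also sends the cost inputs to modellers, so an omission would carry into cost-effectiveness and scale-up results.

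**Working it through.** **1. The plan's own figure.** 12 outpatient providers + 12 outbreak providers + 0 for secondary distribution = 24, as section 5.5 states. The total works only with nobody observed for secondary distribution.

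**2. Tasks against tools.** Under 5.1.4 the staff tasks that belong to delivery are:
- training in swabbing and testing (Overview);
- showing the kits and handing out kits and masks (Recruitment process);
- checking the demonstration back (Exclusion criteria);
- telephone direction for positive contacts (Recruitment process).

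The participant questionnaire asks about the index case's own time and costs. No listed tool for this use case records staff time on any of these tasks.

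**3. Expected volume (5.1.4, Sample size).**
- Index cases: 0.02 × 30,000 = 600.
- Contacts: 600 × (3 household + 2 other close) = 3,000.
- Kits: 3,000 × 2 = 6,000, which matches the Table 1 target.

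**4. Time left unmeasured.** The protocol gives no minutes per index session, so I assume m = 5 to 30. Hours = 600 × m / 60. Minutes per contact = m / 5. Minutes per kit = m / 10, since each index case takes 5 × 2 = 10 kits.

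| m (assumed) | Staff hours | Min per contact | Min per kit |
|---|---|---|---|
| 5 | 50 | 1 | 0.5 |
| 10 | 100 | 2 | 1 |
| 15 | 150 | 3 | 1.5 |
| 20 | 200 | 4 | 2 |
| 30 | 300 | 6 | 3 |

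The per-kit figure does not depend on reaching 600 index cases. It depends on m and on ten kits per index case, and it rises if index cases name fewer contacts.

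**5. Direction.** If this time is not picked up elsewhere, any positive value of m raises the cost per kit distributed, per kit used and per positive diagnosed, and the cost of scale-up, for secondary distribution alone.

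**The case against.** The strongest reply is that the absence of observation does not mean a staff cost of zero. The phrase in 5.5 explains the size of the time-and-motion sample, and Table 1 rules out observations, not costs. Staff time can enter an ingredients costing without being observed. Section 5.5 also has a top-down component, and its own example of a provider to be observed is one who does self-testing as well as PCR. The facility tool in section 5.9 records staffing for each testing service. This stands in part. A reader might infer that staff cost is fixed at zero, and the protocol does not establish that. However, the facility tool is framed around Ag-RDT and PCR testing, and a premise that no staff time exists gives no basis for allocating any to this model.

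Second, the protocol does not say who trains the index case. Section 5.1.4 names the research assistant for screening and consent. The demonstration back is a study eligibility criterion and is absent from the repeated list in section 5.3. This also stands: consent, contact logging and interviews are research time and should stay out. Training and showing the kits are stated independently of that criterion and are part of delivering the model.

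Third, a reader might infer that the costing objectives promise a head-to-head comparison of self-testing with professional testing. They do not. The objectives in 5.5 name one comparison, before against during implementation in outpatients. The self-test comparison is in section 2.3, and the remark there about staff burden concerns integrated services. The comparison is still a declared purpose of the costing, and the full-costing promise does not depend on it.

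Fourth, the amount per kit is small and rests on assumed minutes. That is fair. It bears on the weight of the point and not on its direction.

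**Conclusion.** The point holds in this form. The protocol states a premise that its own procedures contradict, and as a result delivery labour goes unmeasured on the self-testing side only. The likely effect is to understate the unit and scale-up costs of secondary distribution.

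The size is not derivable from the protocol. Fifty to 300 staff hours, or 0.5 to 3 minutes per kit, rests on an assumed 5 to 30 minutes per index session together with the protocol's 600 index cases and ten kits each. It would be tempting to convert this to money or to a share of professional testing time, but neither is supported: the protocol gives no wage for this activity and no duration for a professional test. The point concerns secondary distribution only, because health care worker self-testing is excluded from costing. It should be corrected, but it does not undermine the study.

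**What to change.** In section 5.5, delete the premise that secondary distribution has no staff time, and bring the Table 1 entry into line. State who delivers the index session. Have that person, provider or research assistant, log the minutes spent on training, demonstration back and kit hand-out for a small set of index cases, leaving out consent, the contact log and research interviews. Enter the result as an ingredient cost, with a sensitivity range.

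Adding a code to the existing time-and-motion tool would not be enough. Section 5.1.2 expects 100 × 0.30 × 0.70 = 21 tests per site-day. At 2% positive that is 0.42 index cases. If each of 12 outpatient providers is observed for one day and handles a whole site's testing (both assumptions), about 12 × 0.42 = 5 index sessions would be seen, and none if research assistants deliver them.

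The change costs a short timing log and a slightly less favourable cost for secondary distribution.
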